# BioClock—optimizing Bright Light Therapy for adults with depression: a study protocol for a multicenter randomized clinical trial on treatment strategies, response predictors, and chronobiological and neurobiological mechanisms

**DOI:** 10.1186/s13063-025-08984-7

**Published:** 2025-10-14

**Keywords:** Bright Light Therapy, Chronobiology, Depression, Mood disorders, Melatonin, Sleep, Ecological Momentary Assessment, Magnetic resonance imaging

## Abstract

**Background:**

Bright Light Therapy (BLT) is an effective treatment for various mood disorders, but challenges remain in optimizing its real-world administration, predicting individual responses, and understanding its mechanisms.

**Methods:**

This multicenter randomized controlled trial will enroll 231 patients with unipolar or bipolar depression, all currently experiencing a depressive episode. Participants will be randomized to one of three BLT interventions: (1) traditional home-based BLT, (2) BLT administered in the *LightCafé*—a novel setting promoting social interaction and lifestyle support, or (3) *LightCafé* BLT with personalized timing of both light and darkness by adding the use of blue light blocking glasses. The treatment duration will range from one to three weeks, based on preset definitions of participant’s response. The primary outcome is the change in depressive symptoms, assessed by a blinded rater. Secondary outcomes include subjective and objective sleep measures, circadian rhythm parameters from melatonin patterns and actigraphy, and functional outcomes. Change processes will be assessed using ecological momentary assessments of daily affect and energy levels, light exposure sensors, and via brain imaging.

**Discussion:**

This trial is the first to directly compare different BLT administration models, including a *LightCafé* setting. It aims to identify predictors of BLT response, investigate chronobiological and neurobiological mechanisms, and provide insights to optimize BLT for diverse patient populations. The results will inform clinical guidelines and enhance BLT's accessibility and effectiveness.

**Trial registration:**

Registered on July 14, 2023, at clinicaltrials.gov under number NCT05958940.

**Supplementary Information:**

The online version contains supplementary material available at 10.1186/s13063-025-08984-7.

## Administrative information

Note: the numbers in curly brackets in this protocol refer to SPIRIT checklist item numbers. The order of the items has been modified to group similar items (see http://www.equator-network.org/reporting-guidelines/spirit-2013-statement-defining-standard-protocol-items-for-clinical-trials/).

**Table Taba:** 

Title {1}	**BioClock—Optimizing Bright Light Therapy for Adults with Depression:** A Study Protocol for a Multicenter Randomized Clinical Trial on Treatment Strategies, Response Predictors, and Chronobiological and Neurobiological Mechanisms
Trial registration {2a and 2b}.	The trial is registered on July 14, 2023, at clinicaltrials.gov under number NCT05958940; https://clinicaltrials.gov/study/NCT05958940
Protocol version {3}	Protocol version 3.1, 13–10-2023 Revision Chronology: • 13–10-2023 – version 3.0 Final protocol version after Ethical Approval • 12–05-2023 version 2.0 First submitted version for Ethical Approval • 23–12-2022 – version 1.0 Initial Draft version
Funding {4}	This research is part of the BioClock project (project number: 1292.19.077) of the research program National Science Agenda: Research on Routes by Consortia (NWA-ORC), which receives (partial) funding from the Netherlands Organization for Scientific Research (NWO).

## Introduction

### Background and rationale {6a}

Depressive symptoms place a heavy burden on mood, motivation, and everyday functioning. Yet conventional antidepressants often require weeks to exert their full effects and can burden patients with persistent side effects. Bright Light Therapy (BLT)—which involves repeated exposure to a high-intensity light source—offers a compelling alternative: rapid relief, robust antidepressant impact, and only minimal, transient discomfort. In fact, BLT has now earned a place in clinical guidelines and is widely used in countries across the world—albeit with varied specifications of light intensity, treatment duration, and spectral composition of the light [1–4]. Below, we review BLT’s efficacy across mood disorders, introduce an optimized delivery model, explore predictors of response, and examine the mechanisms underpinning its antidepressant action, all to introduce a multi-center randomized controlled trial (RCT) that investigates the optimization, response prediction, and chronobiological and neurobiological mechanisms of BLT.

### The efficacy of Bright Light Therapy across various mood disorders

The clearest evidence for the efficacy of BLT comes from Seasonal Affective Disorder (SAD). In one of the first trials, Rosenthal and colleagues (1984; *N* = 29) found that 30–60 min of bright light—2500 to 10,000 lx—each morning lifted mood within just 3 to 5 days [5]. Larger, placebo‐controlled studies soon confirmed these results. In a pivotal randomized controlled trial with 96 SAD patients, 1.5 h of 6000‐lux exposure per day produced remission in 61% of participants, compared with just 32% in a dim‐light control group after 3 weeks [6]. Meta‐analyses of around 20 trials (*N*≈1200) report large effect sizes (0.60–1.08), with morning administration and intensities of at least 2500 lx yielding the greatest benefit [7, 8].

BLT’s efficacy, however, extends well beyond SAD. In non‐seasonal major depressive disorder (MDD), early evidence of BLT was mixed [7], but recent meta-analyses now clearly support its use [9, 10]. A meta‐analysis of 20 RCTs (*N* = 881) found a moderate pooled effect (SMD ≈ − 0.4), again highlighting greater efficacy at higher intensities (≥ 7500 lx) and with consistent morning dosing [10]. Even in bipolar depression—where early concerns suggested morning light might trigger mania—a meta‐analysis of 11 studies (*N* = 567) showed significant reductions in depressive symptoms without any increase in manic episodes, provided BLT was used alongside mood stabilizers [11]. Beyond mood disorders, preliminary evidence points to benefits in, e.g., Attention-Deficit/Hyperactivity Disorder (ADHD) [12], Parkinson’s disease [13], dementia [14], and cancer-related fatigue [15]. Across this spectrum of indications, patients typically experience relief within 1 to 2 weeks with minimal side effects. Notable is also the synergistic effects that are achieved when combining BLT with pharmacotherapy [16, 17] underscoring its promise as a transdiagnostic adjunctive intervention.

### From efficacy to optimization

With efficacy well established the challenge shifts from demonstrating that BLT works to refining its delivery. While optimal intensity, spectral composition, and treatment duration remain open questions [9, 10], the greatest impact may come from moving beyond standalone BLT and embedding it within complementary interventions and supportive contexts that together target depressive symptoms. Conventional BLT typically confines patients to their homes or to (semi-)clinical spaces, sitting alone under a bright lamp in an otherwise sterile, low—interaction environment. Although this format reliably delivers the prescribed light dose, it overlooks the potent effects of social engagement [18, 19], behavioral activation [20], and environmental cues [21] on mood and treatment adherence that can amplify and extend BLT’s benefits—transforming it from a solitary task into an immersive, habit-forming therapy. To bring this vision to life, this trial introduces the LightCafé [22]—a BLT delivery model set in a café-style space that feels restorative rather than clinical. Here, instead of solitary lamp setups, participants receive their morning light exposure embedded within a rich psychosocial context. Daily guided social conversations with a therapist foster positive affect and counteract isolation, while lifestyle coaching—from diet and exercise to sleep hygiene and routine building—helps translate acute mood changes into durable behavioral change. This multi-faceted approach is thought to facilitate longer lasting and sustainable change in patients struggling with depressive symptoms.

### Predicting treatment response

The next step in optimization involves more precise therapy selection upfront, as without knowing who benefits most, we risk offering intensive BLT protocols to unlikely responders. However, to date, we lack hypothesis‐driven investigations into which patient characteristics and behaviors predict BLT response. Secondary analyses in SAD cohorts suggest that individuals presenting with atypical features—such as increased appetite, hypersomnia, and a positive diurnal mood variation—alongside higher baseline BMI tend to experience the most rapid and robust improvement with morning light exposure [26, 27]. Those exhibiting melancholic symptoms—psychomotor retardation, early and late insomnia, appetite loss, pervasive guilt, and worse mood upon awakening—often derive little benefit [26]. Similarly, in treatment-resistant inpatients undergoing combined wake and light therapy, early diurnal symptom shifts, evening chronotype, and higher educational history have been linked to both short- and long-term remission [28]. Yet it remains unknown whether these results generalize across the full spectrum of unipolar and bipolar depressions. Clarifying these predictors is crucial: it would empower clinicians to stratify patients by likelihood of response, and ultimately render BLT a more efficient, cost-effective, and patient-centered antidepressant strategy.

### The chronobiological and neurobiological mechanisms underlying BLT

Next, this study aims to examine the mechanisms by which BLT alleviates depressive symptoms, as currently no theory has conclusively explained its effects. The most widely accepted framework—the chronobiological phase-shift hypothesis—proposes that BLT realigns the circadian system with the natural 24-h light–dark cycle [29], correcting rhythm disturbances common in major depressive and bipolar disorders [30–33], and thereby alleviating depressive symptoms. Although robust phase advances following morning BLT have been reliably documented [34], attempts to link these shifts directly to reductions in depressive symptoms have yielded inconsistent results [35–40]. Several other studies further challenge a circadian explanation, suggesting that light exerts its mood-enhancing effects through neural pathways independent of the central clock [17, 41–43], or via directly altering the serotonin release [44, 45]. Consequently, while BLT is often framed as a chronotherapeutic intervention, key questions persist about the true role—and relative importance—of underlying chronobiological mechanisms which we aim to clarify in the current trial.

Light’s impact on sleep quality and energy levels may provide an additional—and potentially contrasting—route by which BLT exerts its antidepressant effects. Up to 90% of depressed patients report insomnia, delayed sleep onset, and fragmented rest at night [46, 47], while many also suffer daytime sleepiness [48]. Controlled trials show that daily morning BLT consolidates sleep, shortens sleep-onset latency, and improves alertness during the day [49, 50], but complicated by the multidirectional associations between mood, sleep, and energy levels [51–53], it remains unclear whether these changes stem from circadian stabilization, light’s direct alerting effects [54, 55], a synergistic interplay of both, or an unknown mechanism. By tracking light exposure, sleep, energy, and mood on a day-to-day level in the current trial, we aim to map how these factors interact with each other over time and gain insight into each one’s role in BLT’s antidepressant mechanism.

Neuroimaging adds a third dimension: though sparse, early studies hint that BLT engages both emotion-processing hubs (amygdala, habenula) and circadian centers (suprachiasmatic nucleus, hypothalamus) [41, 42, 56–58]. Some RCT studies have evaluated the effects of BLT alone or in combination with other chronotherapeutics (e.g., sleep deprivation) in MDD [59, 60], subthreshold depression in adults [57, 61], in young adults [62, 63], or bipolar depression [64, 65]. They used mostly functional neuroimaging techniques to evaluate brain connectivity at rest and reported that weeks (varying between 3 and 8 weeks) of morning BLT restore connectivity within default-mode, frontoparietal, and salience networks—and that these neural changes predicted and correlated with symptom improvement [57, 61, 62, 64]. Interestingly, these studies bring some indications about the use of these neural parameters as potential biomarkers for disease in such that the neural changes found were linked to specific neurotransmitter systems (amongst others serotonin, dopamine) [62], but also to metabolic changes (glutamate/glutamine) [65]. One needs to mention that these studies have a high heterogeneity in study design and sample type used but also in neuroimaging data analysis approach, i.e., some using specific regions of interest and not the whole brain, i.e., amygdala [60], cingulate cortex [62], and cerebellum [61]. Hence, a clear mechanistic model is hard to determine at this stage. In addition, besides evident functional changes after BLT, there are also structural change indications after BLT administration in, e.g., posttraumatic stress disorder (PTSD) [66] and mild traumatic brain injury (mTBI) cohorts [67, 68]. The existing studies suggest that blue-light exposure can increase gray-matter volume and white-matter integrity [66–68].

In the current study, we therefore plan to take a multimodal neuroimaging approach by combining both functional and structural change analysis as well as going from whole brain analysis to specific regions of interest and link it to symptom change pre-post BLT. Hence, we believe that this approach will give a more comprehensive mechanistic model of the neural pattern behind BLT in depression. Furthermore, no study to date has combined precise circadian profiling, sleep metrics, and multimodal imaging in a large, multicenter sample and using the light cafe approach which brings the lacking social component into the depression model—a gap our trial is uniquely poised to fill.

### Objectives {7}

The primary objective of this study is to comprehensively assess and compare the effectiveness of three distinct BLT approaches for the treatment of depressive symptoms: (1) standard home-based BLT (*Light@Home)*, (2) BLT at the *LightCafé (LightCafé)*, and (3) BLT at the *LightCafé* with personalized timing of light and darkness using BBG (*LightCafé* +).

Secondary objectives are:i.The identification of predictors of treatment response, encompassing baseline clinical characteristics, sleep metrics, circadian parameters, and light-related behaviors.ii.Elucidation of underlying mechanisms of BLT’s efficacy by investigating the contribution of circadian rhythm changes, enhancing our understanding of the complex interactions between mood, energy levels, and sleep within the context of BLT and exploration of the neural effects of BLT by studying both functional and structural brain changes before and after treatment.

Importantly, we are not testing BLT’s efficacy for specific diagnostic categories; rather, we ask whether embedding BLT within a rich psychosocial setting and personalizing its timing can amplify and prolong its antidepressant effect, all while unraveling who benefits most and through which pathways. By moving from “Does BLT work?” to “How can we make it work better, for whom, and why?”, this multicenter RCT will lay the groundwork for personalized and embedded BLT protocols and real-world clinical guidelines.

### Trial design {8}

This study constitutes a multi-center, single-blind randomized controlled trial assessing the effects of BLT for individuals with a current depressive episode (either diagnosed with SAD, MDD, or bipolar disorder). The study consists of three phases—the baseline phase, the treatment phase, and the follow-up phase. During the treatment phase, participants will receive BLT through one of three administration strategies—*Light@Home*,* LightCafé*, or* LightCafé* + —with treatment lasting 1 to 3 weeks, depending on their individual response. Baseline assessments occur 1 week prior to treatment, with an additional week for participants undergoing melatonin assessments. Follow-up evaluations occur at 4 weeks, 10 weeks, and 4 months after the start of the treatment.

## Methods: participants, interventions, and outcomes

### Study setting {9}

BLT is administered either at home or in the *LightCafé*, depending on the treatment condition. *LightCafé* locations are distributed across two mental healthcare institutions in the following way:

Mental Health Clinic of Eindhoven and the Kempen (GGzE) in Eindhoven*LightCafé* Ketelhuis Boschdijk, EindhovenLightCafé Lucifer Kennedyplein, Eindhoven*LightCafé* Library Veldhoven, Veldhoven

Leids Universitair Behandel- en Expertise Centrum (LUBEC) in Leiden.*LightCafé *Faculty of Social Sciences, Leiden

### Eligibility criteria {10}

#### General eligibility criteria

Eligibility will be assessed during the intake by study team members trained in administering the MINI International Neuropsychiatric Interview 5.0.0 (M.I.N.I.; [69]). The inclusion criteria are as follows:Age between 18 and 65.Diagnosis of unipolar or bipolar depression (seasonal or non-seasonal) confirmed by the M.I.N.I. [69].Currently experiencing a depressive episode, as indicated by a Quick Inventory of Depressive Symptomatology Self-Report (QIDS-SR; [70]) score of 6 or higher.Proficiency in either Dutch or English is required for questionnaire completion.

Participants are excluded from participation if they:Are currently experiencing a (hypo)manic or mixed episode, as determined by the M.I.N.I. assessment [69].Are presently in a psychotic episode, as determined by the M.I.N.I. assessment [69].Exhibit significant active suicidality, indicated by a score of 10 or higher on the M.I.N.I. module [69].Initiated antidepressant therapy (including medication, psychotherapy, BLT, or other specific depression treatments) within the last 2 months prior to study enrolment.Have a bipolar disorder but are currently not under mood-stabilizing treatment for at least 1 month at the recommended dosage.Have used melatonin or agomelatine in the past month.Are currently using antibiotics.Are currently taking medications that increase light sensitivity.Have travelled across more than one time zone in the past month or during the treatment period.Have travelled to sunny holiday destinations or engaged in outdoor winter sports in the past month.Have pre-existing eye and skin disorders such as retinitis pigmentosa, porphyria, chronic actinic dermatitis, and sun-induced urticaria.Have systemic disorders with potential retinal involvement, such as rheumatoid arthritis and systemic lupus erythematosus.Have color blindness (based on self-report).Worked night shifts within the last three months.Suffer from (retinal) blindness, severe cataracts, or glaucoma.Experience light-induced migraine or epilepsy.Are currently pregnant or have a child Younger than 18 months old.

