#### Who will take informed consent? {26a}

All patients referred to BLT at the study centers are invited to participate in the study. Those expressing interest receive information via email. A follow-up phone call is conducted to confirm their interest and schedule an intake appointment. During the intake, a member of the study team goes over the information letter and informed consent document in detail and answers any questions. If a patient decides to participate, they sign the informed consent and proceed with the diagnostic interview.

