### Relevant concomitant care permitted or prohibited during the trial {11d}

Participants are allowed to continue existing antidepressant treatments alongside BLT, provided these therapies—pharmacological or non-pharmacological—were initiated at least 2 months prior to study entry. This includes antidepressant medications, psychotherapy, EMDR, or other interventions aimed at reducing depressive symptoms. While the initiation of new treatments or dosage adjustments during the study period is discouraged, they are not prohibited. Any such changes will be carefully documented and accounted for in the statistical analysis to control for potential confounding effects.

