### Provisions for post-trial care {30}

In the event of a successful treatment, the opportunity for another round of BLT becomes available 3 months after the last treatment session, provided there are no clinical contraindications, and the final follow-up of the study has been completed. If the treatment is considered unsuccessful, official communication will be sent to the referring healthcare provider, and the responsibility for further treatment will rest with them.

Participants in this study are not provided with research subject insurance coverage, as BLT is a non-invasive treatment associated with a low likelihood of mild and short-term side effects.

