### Recruitment {15}

We intend to include participants year-round for approximately 2 years. The distribution of the recruitment burden is shared between two mental health clinics: GGzE’s aim is to include 171 participants, while LUBEC aims for 60. At GGzE, all individuals referred for BLT are approached for potential participation. Previous light therapy studies conducted at this center with the same enrolment strategy have achieved inclusion rates of approximately 100 participants per year. Given that this study is considered more extensive than previous research, we anticipate it will take approximately 2 years to reach the targeted enrolment of 171 participants. At LUBEC, BLT is offered for the first time, and only in conjunction with study participation. Recruitment efforts involve the collaboration with primary care and secondary mental health institutions for the referral of patients.

The rate of participant accrual is reviewed every half year. The number of participants who consented but did not qualify and the number of qualified, enrolled participants who dropped out will also be examined to detect patterns of insufficient recruitment rates. These will be addressed with modified recruitment strategies so that we can meet our recruitment goals.

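### Prior BLT is screened by its start date alone, so a patient whose own BLT began more than two months ago and is still running may be randomised and continue it in any arm

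*Protocol article*

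**What the plan says.** In the protocol article, General eligibility criteria, a person is excluded if they "Initiated antidepressant therapy (including medication, psychotherapy, BLT, or other specific depression treatments) within the last 2 months prior to study enrolment". BLT is named there and gets the same test as medication and psychotherapy: the date it began.

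The section on relevant concomitant care {11d} is the counterpart: "Participants are allowed to continue existing antidepressant treatments alongside BLT, provided these therapies—pharmacological or non-pharmacological—were initiated at least 2 months prior to study entry". Its scope is left open: "This includes antidepressant medications, psychotherapy, EMDR, or other interventions aimed at reducing depressive symptoms". BLT is neither listed nor carved out.

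Elsewhere the same exclusion list tests recent exposure instead of start date. One item reads "Have used melatonin or agomelatine in the past month". Another looks back one month for sunny holidays and outdoor winter sports.

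On the source population, the consent section says "All patients referred to BLT at the study centers are invited to participate in the study". Table 1 records current medications and therapies at Intake, PT1, F1 and F2.

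**The concern.** A start-date test suits background therapy, because a treatment begun long enough ago is taken to have reached a steady state. Applied to the trial's own intervention it works the wrong way round: the longer a patient has already been on BLT, the more clearly they pass.

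Three things are at stake.

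- **The setting and timing contrast.** The primary objective compares home BLT with LightCafé BLT, with and without personalised timing. A LightCafé participant who also uses light at home receives both settings. A LightCafé+ participant with additional light at other times does not receive the timing assigned.
- **The baseline.** For someone already on BLT, the baseline MADRS, melatonin onset (DLMO) and MRI are not pre-BLT values.
- **The uncontrolled comparisons.** The main MRI analysis is pre versus post with no comparison between arms, and the circadian models also interpret the effect of time by itself. Randomisation gives no protection there.

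**Working it through.** **Step 1. Apply the text to one case.** Take a patient whose own BLT began 10 weeks (70 days) before enrolment and is still in use. Two months is taken as 61 days.

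| Rule | Test | Result |
|---|---|---|
| Prior-treatment exclusion | Started within 61 days? 70 > 61 | Not excluded |
| Concomitant care {11d} | Existing antidepressant treatment, drug or non-drug, started at least 2 months before entry? | May continue |
| Melatonin or agomelatine; sunny holidays | Recent use or exposure | Does not reach BLT |

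**Step 2. Look for a passage that closes the gap.**

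- No criterion excludes BLT in current use, and none sets an interval from the last BLT session.
- The stratification factors are chronotype, diagnosis and melatonin participation. Prior or current BLT is not among them.
- The undertaking in {11d} to document and adjust covers treatments started, or doses changed, during the study. It does not cover a treatment that simply continues.
- The additional analyses {20b} model medication type and dose, and measure adherence to the prescribed sessions. Non-trial BLT is not named.

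**Step 3. See how far the gap extends to completed courses.** Days between the end of a course and enrolment, for a course begun exactly 61 days before, are 61 − 7 × weeks:

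- 1 week: 61 − 7 = 54 days
- 2 weeks: 61 − 14 = 47 days
- 3 weeks (the trial's maximum): 61 − 21 = 40 days
- 8 weeks: 61 − 56 = 5 days

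So a course of the trial's own length that ended within about the last five weeks must have started inside the window, and it is excluded. The real gap is ongoing use.

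**Step 4. Scale the possible dilution.** The plan's own figure comes first. The inputs from the sample-size section are f = 0.25, alpha 0.05, power 0.90 and three arms. Using a noncentral F with 2 and N − 3 degrees of freedom and λ = f²N, the smallest balanced N is 207 (power 0.902). At the stated 210, λ = 0.0625 × 210 = 13.125 and power is 0.907. This is close to the plan's 210.

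The share p of participants on their own BLT is not in the document, so p is an assumption. Suppose also, as an extreme, that these participants show no arm difference at all. Then f becomes 0.25 × (1 − p):

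| Assumed p | f | λ at N = 210 | Power at N = 210 | N for 90% power |
|---|---|---|---|---|
| 0 | 0.250 | 13.13 | 0.907 | 207 |
| 2% | 0.245 | 12.61 | 0.894 | 216 |
| 5% | 0.2375 | 11.85 | 0.874 | 228 |
| 10% | 0.225 | 10.63 | 0.834 | 255 |
| 20% | 0.200 | 8.40 | 0.733 | 321 |

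The table shows how the loss would grow with p. It does not estimate p, and no row is better supported than another.

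**The case against.** The strongest reply has four parts.

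- **The reading is strained.** The concomitant-care section speaks of treatments used alongside BLT, so counting BLT among them makes it a treatment permitted alongside itself. The authors probably did not intend this. But the exclusion criterion itself classes BLT as an antidepressant therapy, and nothing in {11d} takes it out again. Site staff must apply the text as it stands.
- **Such patients should be rare.** Candidates are people being referred for BLT, and few will already have been on it for months. At the second site, "At LUBEC, BLT is offered for the first time, and only in conjunction with study participation". This stands and limits the size of the problem. It does not remove it, since the Discussion itself says that many patients already receive BLT at home.
- **Such use can be detected.** Therapies are recorded at Intake, and light sensors are worn from baseline through the week after treatment. This also stands, but no rule says what to do when such use is found.
- **An article is condensed.** That excuses missing detail. Here the criterion is printed and names BLT, and the issue is the test it applies.

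A reader might infer more than the document supports:

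- *Patients who have just finished a course are admitted.* For courses of one to three weeks, Step 3 shows a gap of at least about 40 days.
- *The interval in post-trial care conflicts with the criterion.* The statement that "the opportunity for another round of BLT becomes available 3 months after the last treatment session" is a re-treatment provision conditional on completed follow-up. It is not a washout.
- *Former participants can be randomised again.* Nothing says so. This would be an argument from silence.
- *Dose changes go unhandled.* Changes during the study are to be documented and adjusted for, and medication dose enters the models as a covariate.
- *A definite share of the MRI sample is affected.* All MRI participants come from the site that had not offered BLT before, so earlier BLT would have to come from elsewhere. No count can be supported.

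**Conclusion.** The point holds in a limited form. Taken together, the exclusion criterion and the concomitant-care rule admit a patient with ongoing BLT begun more than two months earlier and allow it to continue in any arm, and no other part of the article closes this.

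The direction of the expected harm is dilution. Randomisation spreads such patients over the three arms, so the text does not support a claim of systematic advantage for one arm or of contamination as an established fact. In the uncontrolled pre-post analyses, a baseline taken on BLT would tend to understate the change.

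The size is unknown and probably small. The power figures rest on an assumed share and an assumed complete loss of contrast. The textual finding depends on neither. It is worth correcting because the change is cheap and protects both the primary contrast and the meaning of baseline.

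**What to change.** 1. In General eligibility criteria, take BLT out of the start-date clause and give it its own use-based criterion: BLT in use at Intake, or received within an interval that the sponsor sets, counted from the last session. The list already uses this form for melatonin and agomelatine.
2. In Relevant concomitant care {11d}, state explicitly whether non-trial BLT counts as permitted continuing treatment, so that the two sections agree.
3. Enrolment has been open since February 2024. For those already randomised, use the Intake therapy record to flag anyone on BLT at entry, and add a sensitivity analysis of the primary outcome and the pre-post analyses without them.

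The cost is a wording amendment, one question at Intake where therapies are already recorded, and one extra analysis. A few patients may be deferred or lost to recruitment. The planned sample size does not change.
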